#### 7.4.3 Vital Signs

Mean  $\pm$  standard deviation, maximum, minimum, and median will be used to describe the measurements and changes before and after treatment.

A listing of vital signs by subject for all visits will be provided.

#### 7.4.4 Laboratory Measurements

Mean  $\pm$  standard deviation, maximum, minimum and median will be used to describe the measurements and changes of hematology, blood chemistry and coagulation function before and after treatment. Crossover classification table will be used to describe the normal and abnormal changes before and after treatment.

Urinalysis: crossover classification table will be used to describe the normal and abnormal changes before and after treatment.

The proportion of subjects with “abnormal and clinically significant” changes will be described among subjects with abnormal changes, in which the clinical significance of the abnormality will be determined by the investigator. A listing of abnormalities after treatment will be provided.

Listings of hematology, urinalysis, blood biochemistry and coagulation function data by subject at all visits will be provided.

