### **Safety Analysis**

Safety analysis will be tabulated and analyzed by descriptive statistics based on the Safety Set (SS), including AEs, laboratory tests, vital signs, electrocardiogram data, etc.

AEs will be coded according to MedDRA. AEs will be summarized by treatment group. The incidences of AEs, drug-related ADRs, SAEs, etc. will be summarized by system organ class (SOC) and preferred term (PT), and relevant adverse events will be tabulated. Incidences (number of subjects: number of subjects with at least one AE) will be calculated by SOC and PT; if a subject experiences the same AE for many times, the AE with the highest severity will be counted.

Other safety variables will be summarized using descriptive statistics. The mean, standard deviation, maximum, minimum and median will be used to describe each measurement and change from baseline. The frequency and percentage will be used to describe categorical

variables.

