## 4. Safety Variables

### 4.1 Adverse Events

Treatment-emergent adverse event (TEAE) is defined as any untoward medical condition that occurs after a subject receives the drug, which may manifest as symptoms, signs, diseases, or laboratory abnormalities, but does not necessarily have a causal relationship with the investigational product. AEs include, but are not limited to, the following:

- 1) Worsening of pre-existing (before enrollment) medical conditions/diseases (including worsening of symptoms, signs, laboratory abnormalities);
- 2) Any new AEs: any new adverse medical conditions (including symptoms, signs, newly diagnosed diseases);
- 3) Abnormal and clinically significant laboratory values or results.

The study personnel should record in detail any AE, including: AE name, time of onset,

severity, relationship to the investigational product, end time, action taken with the investigational product, and final results and outcome.

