#### 4.2 Treatment-related Adverse Events

The investigator should comprehensively assess and judge the relationship between the AE and the investigational product according to the five-level classification of "related, possibly related, unlikely related, unrelated, not determined". "Related", "possibly related" and "not determined" adverse events are listed as treatment-related adverse events (TRAEs), the sum of which will be the numerator to calculate the incidence of TRAEs, while the number of all subjects for safety evaluation is the denominator.

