### 6.3 Safety Set (SS)

It Includes all enrolled subjects who received the study drug.

This set will be used for safety analysis. Treatment groups will be based on actual grouping.

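### Clinically significant laboratory, ECG and examination changes are given only as a share of subjects with abnormal changes, so the percentages shown by arm are not risks and can misstate arm differences

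*Combined protocol and SAP*

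**What the plan says.** SAP 7.4.4 (laboratory), 7.4.5 (ECG) and 7.4.6 (physical examination) carry the same sentence. The share of subjects whose change is both abnormal and judged clinically significant "will be described among subjects with abnormal changes"; the judgement is left to the investigator. None of the three sections adds a proportion out of all subjects tested or out of the Safety Set.

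Elsewhere the SAP bases safety on everyone treated. SAP 6.3 says of the Safety Set: "This set will be used for safety analysis. Treatment groups will be based on actual grouping". SAP 4.2 defines the incidence of treatment-related adverse events with a full denominator: "while the number of all subjects for safety evaluation is the denominator". The three sentences depart from that convention and give no reason.

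Three other provisions bear on the weight of the point:

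- The same sections plan shift tables ("Crossover classification table will be used to describe the normal and abnormal changes before and after treatment"), a listing of post-treatment abnormalities and by-subject listings.
- The protocol's Safety Analysis section makes these variables descriptive: "Other safety variables will be summarized using descriptive statistics".
- SAP 4.1 counts "Abnormal and clinically significant laboratory values or results" as adverse events, so these also enter the incidence tables of SAP 7.4.2.

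**The concern.** Whether a subject has an abnormal result after dosing is known only after randomisation and may itself depend on the drug. Restricting the denominator to such subjects selects a different kind of subset in each arm. The percentage answers a narrow question: of those with an abnormal change, what fraction did the investigator call clinically significant? A reader of a safety table will usually take it for the chance that a treated subject has a clinically significant change.

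At stake is how the laboratory, ECG and examination tables read for the two SHR8554 doses, morphine and placebo. The ECG table deserves most care. SAP 7.4.5 plans means, a normal/abnormal shift table, this percentage and listings, but no summary of QTc by category, although the protocol's 12-Lead ECG section calls for repeat tracings when QTc rises by more than 30 ms.

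**Working it through.** **Inputs.** The denominator rule is that of SAP 7.4.4 to 7.4.6. The documents give no abnormality or clinical-significance counts for this trial, so every such count below is an assumption. The only figure taken from the plan is the arm size.

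**Arm size, reproduced.** The Sample Size section assumes means of 88 and 70 and SDs of 45 and 40, with two-sided α = 0.05 and 90% power.

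- Pooled SD = √((45² + 40²)/2) = 42.57 and the difference is 18. The normal-approximation formula for two means gives 118 per group.
- 118/(1 − 0.10) = 131.1, rounded up to 132. Then 4 × 132 = 528.

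Both agree with the plan. N = 132 is used below as the full denominator.

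**Identity.** Write CS for clinically significant. Every CS change is also an abnormal change, so within an arm

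P(CS | abnormal) = P(CS) / P(abnormal).

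Dividing one arm by the other:

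ratio shown under the SAP rule = (true risk ratio) / (ratio of abnormality rates).

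The ratio is right only when the abnormality rates are equal. The level is right only when every subject is abnormal.

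**Equal risk, unequal abnormality (assumed).** Risk is 5% in both arms, with 20% abnormal in one and 60% in the other.

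- 0.05/0.20 = 25%.
- 0.05/0.60 = 8.3%.

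The risks are the same, yet the table suggests a threefold difference. If 20% were abnormal in both arms, both would show 25%. The ranking is then right, but the level is 1/0.20 = 5 times the risk.

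**Assumed counts, N = 132 per arm.**

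| Case | Active abnormal / CS | Placebo abnormal / CS | SAP share | Share of all 132 | Effect |
|---|---|---|---|---|---|
| a | 60 / 6 | 30 / 3 | 10.0% vs 10.0% | 4.5% vs 2.3% | doubling hidden |
| b | 60 / 6 | 20 / 4 | 10.0% vs 20.0% | 4.5% vs 3.0% | direction reversed |
| c | 80 / 8 | 40 / 8 | 10.0% vs 20.0% | 6.1% vs 6.1% | difference created |
| d | 30 / 6 | 30 / 3 | 20.0% vs 10.0% | 4.5% vs 2.3% | ratio 2.00 on both scales |
| e | 100 / 10 | 90 / 9 | 10.0% vs 10.0% | 7.6% vs 6.8% | ratio 1.00 against a true 1.11 |

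The identity accounts for each row. In case b, for example, the true risk ratio is 6/4 = 1.5 and the abnormality ratio is 60/20 = 3, so the ratio shown is 1.5/3 = 0.5. Cases d and e show that the distortion vanishes or is small when the arms have equal or similar abnormality rates.

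**The case against.** The best defence is that nothing rests on these percentages and that the missing information is mostly available elsewhere. Much of this stands.

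- **Only a description.** No between-arm test or effect estimate is planned for these variables. A reader might infer that the trial compares arms formally on a subset that randomisation no longer protects. The documents do not support that, since the percentages are simply tabulated side by side. A descriptive percentage can still be misread.
- **Adverse event tables.** A reader might infer that these are the only percentages planned for clinically significant findings. They are not. Clinically significant laboratory values are adverse events by definition and are summarised by system organ class and preferred term on the Safety Set. ECG and examination findings are not named in that list, but the list is not exhaustive, and the phase 2 study reported ECG findings as adverse events by arm. This route is partial. It runs by preferred term and not by parameter, it depends on the investigator recording an event, and the protocol excludes surgery-related events from adverse events.
- **Recoverable counts.** SAP 7.1 requires frequencies beside percentages, so the numerator will be visible and can be divided by the number tested. The shift tables help less, because as described they separate normal from abnormal and do not show clinical significance.
- **Similar abnormality rates.** Post-treatment laboratory tests and physical examination fall between 24 h and D4 ± 1 after abdominal surgery, which all arms undergo. It is plausible, though not documented, that surgery drives many abnormalities equally. That would preserve the ranking, but the percentage would still exceed the risk.
- **A legitimate quantity.** The share judged clinically significant among abnormal results is a fair descriptive statistic. It is not a substitute for the risk.

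**Conclusion.** The point holds as a minor one. The rule as written produces percentages that are not risks, and it can hide, create or reverse a difference between arms when abnormality rates differ. The size is governed by the ratio of abnormality rates. At equal 5% risk, a threefold difference in those rates appears as 25% against 8.3%, and with equal rates only the level is wrong. All these rates are assumed, and the documents give no ground for expecting any particular imbalance.

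A reader might also infer that an arm with many mild abnormalities will always look safer than one with few. That does not follow. It happens only if clinically significant counts do not rise in proportion to abnormal counts; in case a they do, and the shares are equal.

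The primary endpoint, its test and the sample size are unaffected.

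**What to change.** In SAP 7.4.4, 7.4.5 and 7.4.6:

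1. Report per arm the number and percentage of subjects with a clinically significant post-treatment abnormality. Use as denominator all Safety Set subjects with a baseline and at least one post-baseline result for that parameter.
2. State how subjects already clinically significantly abnormal at baseline are counted.
3. Keep the shift tables and listings as planned.
4. If the share among abnormal subjects is wanted, show it as a second line with its n.

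The cost is SAP wording in three places and one extra table line. No new data are needed.

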#### 7.4.5 Electrocardiogram

Mean  $\pm$  standard deviation, maximum, minimum and median will be used to describe the measurements and changes of heart rate, PR, QT and QTc intervals before and after treatment.

Crossover classification table will be used to describe the normal and abnormal changes before and after treatment. The proportion of subjects with “abnormal and clinically significant” changes will be described among subjects with abnormal changes, in which the clinical significance of the abnormality will be determined by the investigator. A listing of abnormalities after treatment will be provided.

A listing of 12-lead ECG data by subject at all visits will be provided.

#### 7.4.6 Physical Examination

Crossover classification table will be used to describe the normal and abnormal changes before and after treatment. The proportion of subjects with “abnormal and clinically significant” changes will be described among subjects with abnormal changes, in which the clinical significance of the abnormality will be determined by the investigator. A listing of abnormalities after treatment will be provided.

A listing of physical examination data by subject for all visits will be provided.

#### 7.4.7 Transdermal Oxygen Saturation (SpO2)

Mean  $\pm$  standard deviation, maximum, minimum, and median will be used to describe the measurements and changes before and after treatment.

A listing of SpO2 data by subject for all visits will be provided.

#### 7.4.8 Concomitant Medications and Concomitant Non-drug Therapies

The use of concomitant medications during the study and the frequency of use of each drug will be summarized. Concomitant medications will be coded by ATC classification, and frequencies will be summarized and described by Anatomical Classification (ATC Level 1 coding) and Therapeutic Classification (ATC Level 2 coding).

Concomitant non-drug therapies during treatment: the frequency and constituent ratio will be calculated.

A listing of concomitant medications and concomitant non-drug therapies used by

subjects will be provided.

### 7.5 Sensitivity Analysis

- Time-weighted Sum of Pain Intensity Differences at rest up to 24 h after starting infusion of loading dose of investigational product (SPID24). (Score not imputed after rescue analgesia)
- Time-weighted Sum of Pain Intensity Differences at rest up to 24 h after starting infusion of loading dose of investigational product (SPID24). (Randomized population)

### 7.6 Subgroup Analysis

NA

### 7.7 Other Analysis

NA

## 8. Statistical Analysis Software

The statistical analysis will be performed using SAS 9.4.

## 10. Appendixes
